#### Patient Health Questionnaire 9 (PHQ-9)

The PHQ-9 will be used to measure the severity of the participants’ depressive symptoms during pre-test and post-tests [26]. It will be used for screening and for measuring change in depressive symptoms over the period of the intervention/waiting period. The questionnaire has nine items measured on a 4-point scale ranging from 0 (not at all) to 3 (nearly every day). The total score ranges from 0 to 27 with a score of ≤ 4 indicating minimal or no depressive symptoms, 5–9 mild depressive symptoms, 10–14 moderate depressive symptoms, 15–19 moderately severe depressive symptoms, and 20–27 severe depressive symptoms. A total score is obtained by adding the scores of the nine items. The scale has been widely used in measuring depressive symptoms and has good psychometric properties [26]. In addition, the PHQ-9 is often used with PLH and has been found to be highly reliable [37].

#### Patient Health Questionnaire 2 (PHQ-2)

The PHQ-2 [38] will be used to screen participants at the hospitals for depressed mood. The scale consists of the first two items of the PHQ-9 measured on a 4-point scale ranging from 0 (not at all) to 3 (nearly every day). The sum score ranges from 0 to 6 with higher scores indicating significant depressive symptoms. A total score is obtained by adding the scores of the two items. For the proposed study, any participant who scores above zero will be referred, after consent, to the study for further screening. The scale has shown good psychometric properties [38].

#### Patient Health Questionnaire 4 (PHQ-4)

The PHQ-4 [39] will be used to measure symptoms of depression and anxiety during the intervention or waiting period for the control group. The scale consists of the first two items of the PHQ-9 and the first two questions of the GAD-7 measured on a 4-point scale ranging from 0 (not at all), 1 (several days), 2 (more than half the days), to 3 (nearly every day). The sum score ranges from 0 to 12 with higher scores indicating significant depressive symptoms. A total score is obtained by adding the scores of the four items [39]. The PHQ-4 has been shown to be highly reliable in screening both depression and anxiety [39, 40].

#### Physical tension questionnaire

One item from the physical tension questionnaire (developed by [name] and [name], unpublished) will be used to assess physical tension. The item “How often do you experience tight (or tense) feelings in your body?” was selected based on item-total correlations from our finding from a previous study that investigated the prevalence and risk factors of depressive symptoms, needs of PLH, and feasibility of an intervention program. The item is measured on a 5-point scale from 1 (always), 2 (often), 3 (sometimes), 4 (rarely), to 5 (never). A higher score indicates less physical tension.

#### Behavioral Activation for Depression Scale (BADS)

The BADS is a scale consisting of 25 items that are measured on a 7-point scale ranging from 0 (not at all) to 6 (completely). The scale is used to measure weekly changes in depression-related behaviors. It measures changes in activation, avoidance/rumination, work/school impairment, and social impairment. The scale has been reported to have good psychometric properties [30]. We will use an item from the subscale of the BADS (activation) to measure how focused the participants are on achieving certain goals and completing planned activities in the past week. The item “I was an active person and accomplished the goals I set out to do” was selected based on item-total correlations from the baseline study data and is measured on a 7-point scale ranging from 0 (not at all) to 6 (completely). Participants who score highly have greater levels of activation.

#### Cognitive Emotion Regulation Questionnaire-short version (CERQ-short)

The CERQ-short is an 18-item questionnaire used to measure cognitive coping strategies [31]. Based on our previous study findings, four subscales of the CERQ-short (rumination, catastrophizing, positive refocusing, and refocus on planning) will be used to measure the cognitive coping strategies used by the participants in relation to living with HIV [31]. The items are measured on a 5-point Likert scale ranging from a score of 1 (almost never) to a score of 5 (almost always). Each subscale has a minimum score of 2 and a maximum of 10. The subscales will be scored by adding the scores on the two items of each subscale. Higher scores on a subscale total indicate frequent use of the coping strategy. All of the subscales have been found to have good psychometric properties [31].

#### Behavioral Emotion Regulation Questionnaire (BERQ)

The BERQ is a 24-item scale that measures behaviors that PLH engage in to cope with having HIV [32]. Based on our previous study findings, behavioral coping strategies will be measured using two items from one subscale of the BERQ (withdrawal). Items were selected based on item-total correlations. Each item is measured on a 5-point Likert scale ranging from 1 (almost never) to 5 (almost always). The scores range between 0 and 10, and the total score is calculated by adding the scores of the two items of the subscale. Higher scores on the subscale total indicate frequent use of the coping strategy. All subscales of the BERQ have been found to have good internal reliability with alpha ranging from 0.86 to 0.93 [32]. In our baseline study, the alphas ranged between 0.71 and 0.84 (Table 1).

#### Generalized Anxiety Disorder 7 (GAD-7)

The GAD-7 questionnaire is used to measure the severity of generalized anxiety disorder [33]. We will use this scale to measure participants’ severity of anxiety symptoms. The scale has seven items that use a 4-point scale ranging from 0 (not at all) to 3 (nearly every day). The total scale is obtained by adding the scores of all seven items. Scores range between 0 and 21. Participants with higher scores experience more symptoms of anxiety. The scale has adequate psychometric properties [33].

#### Life Events Scale

The 17-item Negative Life Events Scale [34] was shortened to eight items and will be used to assess the experience of negative life events in the participants’ life in the past year (e.g., death of a significant other, divorce/breakup of a longstanding relationship, violence within family or partner relationship). The items were selected based on events known to correlate most strongly with depressive symptoms [41]. Furthermore, we included only life events that are relevant to our sample. The items will be measured on a 2-point scale (No or Yes), and a total score will be computed by adding all the response scores.

#### Self-efficacy

Self-efficacy will be assessed using one item from the 10-item HIV-specific self-efficacy questionnaire ([name] and [name], “Self-efficacy questionnaire,” unpublished), according to the original questionnaire [42]. The item “I am confident that I can deal with having HIV” was selected based on item-total correlations. The item is measured on a 5-point Likert scale ranging from 1 (totally disagree) to 5 (totally agree). Higher scores indicate high self-efficacy (confidence in the ability to cope with having HIV).

#### Goal Disengagement and Reengagement Scale

Goal adjustment will be assessed using the six-item Reengagement subscale of the Goal Disengagement and Reengagement Scale [35]. The subscale was adapted to measure the participants’ ability to reengage in new goals following disengagement from goals they can no longer achieve due to the HIV (e.g., “If I have to stop pursuing an important goal in my life because I have HIV, I seek other meaningful goals”). The items are measured using a 5-point Likert scale ranging from 1 (totally disagree) to 5 (totally agree). A high score represents more goal reengagement. We included an additional item “I have already found new goals.” This item will not be used to calculate the total scores of the subscale.

#### Alcohol and substance use

A four-item questionnaire that measures the frequency of using alcohol, soft drugs, hard drugs, and sedatives in the past 3 months was developed based on the second item of the Alcohol, Smoking and Substance Involvement Screening Test (ASSIST) [36]. The ASSIST has been validated as a screening tool for alcohol and substance use cross-culturally [36]. The four-item questionnaire adapted for this study will be used to measure the frequency of alcohol and substance use (e.g., “In the past 3 months, how often have you used alcohol?”) The items will be measured on a 5-point scale ranging from 1 (never), 2 (once/twice), 3 (monthly), 4 (weekly), to 5 (daily/almost daily). Higher scores indicate frequent use of alcohol or a substance.

#### Social support

Social support will be measured by a self-designed item that measures the level of satisfaction with support received. The item “Are you satisfied with the extent to which people around you try to support you in living with HIV?” will be measured on a 5-point scale ranging from 1 (not at all) to 5 (certainly). High scores indicate satisfaction with the social support provided.

#### Demographic variables and other information

A self-designed questionnaire will be used to collect demographic information that will be used to describe the study sample. The questionnaire will collect personal information at T0 (e.g., gender, age, level of educational), past episodes of depressive and anxiety symptoms, any psychological/psychiatric treatment received for the symptoms, and physical health. Information regarding the HIV infection will also be collected through the use of a questionnaire at T0. We will ask the participants to indicate when they were diagnosed, cluster of differentiation 4 (CD4) cell count, viral load, whether they are taking ART, adherence to medication, and how satisfied they are with their HIV treatment. Questions regarding medication use for psychological problems and psychological treatment received since the beginning of the study will be asked at T0, and any changes in medication and treatment will be reported during follow-up.

#### Motivation to start with the intervention

Participants will be asked one question related to their motivation to start the intervention (“How motivated are you to start the intervention?”). Participants will rate their motivation to start the intervention on a scale from 1 (not motivated at all) to 10 (highly motivated).

#### Compliance

We will measure whether participants are adhering to the program. To assess for compliance with the program, we will ask the participants three questions to check whether they have read the information in the booklet about lessons and whether they followed the exercises in the booklet (“Which lesson(s) have you done since the last time you completed a questionnaire?”, “Did you read the text and explanation in the lessons?”, and “How often have you performed the following exercises since the last time you completed a survey?”). Participants can answer (Yes, completely), (Yes, partly), or (No, not at all) or tick lessons from the list provided for the last question. Compliance will be measured at three different points during the intervention and at post-test. Compliance will also be monitored through participant’s calls with the coach.

#### Dropout and reasons for dropout

We will take record of all participants who are no longer following the intervention and those who have no interest in completing the questionnaires. Participants are expected to complete questionnaires at three different points during the intervention/waiting period and at post-test. Participants will be asked the reason(s) for dropping out of the study.

#### User satisfaction questionnaire

A self-designed questionnaire with 31 open and close-ended questions will be used to collect information regarding participants’ satisfaction with the self-help program as well as their coach. The questionnaire will ask participants to evaluate the intervention as well as the support received from the coach assigned. Participants in the control condition will be asked 11 questions to evaluate their support from the coaches only. The responses will help in adjusting the program where necessary.

### Statistical analyses

Data will be analyzed using an intention-to-treat (ITT) analysis [43]. We will use a two-tailed alpha of 0.5 for significance testing. To investigate baseline differences between conditions, we will use chi-square and analysis of variance (ANOVA) tests for categorical and continuous variables, respectively.

Differences between groups in depressive symptoms from pre-test to post-tests will be investigated using longitudinal multilevel regression analyses (LMRAs) [44]. We will adopt a two-level model where time and group will be included as fixed effects and the slopes for time and the intercept as random effects. The between-group analysis will include the pre-test, post-test, and follow-up. To investigate the long-term effects of the intervention, we will include the pre-test, post-test, and follow-up in the within-group analysis. To estimate the effects in the model, we will employ a maximum likelihood estimation type. We will also study the differences between participants who followed the intervention to the end and those who dropped out with chi-square tests and ANOVAs.

Furthermore, Cohen’s *d* will be used to calculate within- and between-group effect sizes. Effect sizes less than 0.20 are regarded as having a small effect, 0.50 a medium effect, and 0.80 a large effect [45]. We will also explore clinically significant differences for individual change in depressive symptoms. Individual change scores of 5 or more for the PHQ-9, from pre-test to post-test and follow-up, will be regarded as clinically significant [46]. The same approach will be used to examine pre-treatment versus post-treatment changes with regard to all secondary outcomes.

We will examine moderators of the treatment outcome using LMRA. We will enter potential moderators individually. Additionally, we will employ the latent difference score model for mediation analysis [47].

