### Sample size

To determine the sample size needed for the RCT, we performed a power analysis using the 14th Edition of the Power Analysis and Sample Size Software (PASS) [27]. It was calculated that each group should consist of 64 participants (effect size = 0.50, alpha = 0.05, and power = 0.80). Similar studies have recorded a dropout rate of 15%; therefore, at least 75 participants should be allocated to each group. Taking into account the possibility of further dropout at follow-up, a total of 200 participants will be recruited for the RCT.

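### The analysis section sets the two-tailed significance level at 0.5, ten times the 0.05 used to size the trial; almost certainly a misprint, but it is the only significance threshold given for the analysis

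*Protocol article*

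**What the plan says.** The protocol article gives a significance level in two places.

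- **Statistical analyses**, opening paragraph: "We will use a two-tailed alpha of 0.5 for significance testing". The sentence is not limited to any one analysis. The tests described after it are the baseline comparisons, the longitudinal multilevel regression of depressive symptoms, the comparison of completers with dropouts, and the moderator analyses.
- **Sample size**: "It was calculated that each group should consist of 64 participants", with the inputs "effect size = 0.50, alpha = 0.05, and power = 0.80". This section does not say whether its alpha is one- or two-tailed.

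The Statistical analyses section also treats a PHQ-9 change of 5 points or more as clinically significant. That is a criterion for change in an individual and does not serve as a test threshold.

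**The concern.** The two figures differ by a factor of ten (0.5 / 0.05 = 10), and the unusual one stands in the section that governs the analysis. The article does not reconcile them.

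The significance level is the part of a plan that most needs to be fixed before data exist. Here an analyst who follows the analysis section would apply a threshold that gives almost no protection against chance findings. An analyst who uses 0.05 would depart from the written text. If the figure is corrected only after results are known, it can no longer be shown that the correction was independent of them. The article says that the program will be implemented in Botswana if it is found effective, and may be adapted for other countries, so the rule for finding it effective has consequences.

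**Working it through.** **Inputs.** From Sample size: effect size d = 0.50 (standardized, so SD = 1), alpha 0.05, power 0.80, 64 per group, 15% dropout, 200 recruited in total. From Statistical analyses: alpha 0.5, two-tailed.

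**1. Reproduce the plan's own figure.** For two equal groups, the normal approximation is n per group = 2(z₁₋α/₂ + z₁₋β)² / d².

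- Two-sided 0.05: 2(1.960 + 0.842)² / 0.25 = 62.8, so 63. The exact two-sample t-test gives 63.77, so **64**, the stated figure. Power at 64 per group is 80.1%.
- One-sided 0.05: 50 (normal) or 51 (t-test). This does not reproduce 64.
- Two-sided 0.5: 2(0.674 + 0.842)² / 0.25 = 18.4, so 19. The exact t-test gives 17.1, so **18**; it is slightly lower because it also counts rejections in the wrong direction. This does not reproduce 64.

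Of these readings, only the two-sided 0.05 yields the planned size.

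**2. Error rates if 0.5 is applied literally.** The critical value is |z| > 0.674 instead of |z| > 1.960.

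| Per test of a true null | alpha 0.5 | alpha 0.05 |
|---|---|---|
| Any significant result | 50% | 5% |
| Significant in favour of the booklet (half of the above) | 25% | 2.5% |

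**3. Illustration on the SD scale.** The smallest significant difference in a two-sample t-test is t₁₋α/₂ × √(2/n).

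| n per arm | √(2/n) | alpha 0.5 | alpha 0.05 |
|---|---|---|---|
| 64 | 0.177 | 0.120 SD | 0.350 SD |
| 85 (assumed) | 0.153 | 0.104 SD | 0.303 SD |

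The 85 is not in the article. It is 200 split equally, less 15%: 100 × 0.85 = 85. The article expects further dropout at follow-up, so 85 would not apply there.

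**4. Power.** With d = 0.50 and 64 per arm, t-test power is about 98.5% at alpha 0.5, against 80.1% at alpha 0.05.

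Steps 3 and 4 describe a t-test. The planned analysis is a multilevel model with random intercept and slope over three assessments, so these values show the scale of the effect and are not that model's own thresholds.

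**The case against.** The strongest reply is that this is plainly a misprint and that nobody would run the analysis at 0.5. The first half stands: step 1 of the working shows that the trial was sized at a two-sided 0.05, so the article itself indicates which figure was meant. The realistic harm is therefore a wrong prespecified threshold on record, with ambiguity until it is corrected. Literal use of 0.5 is unlikely. The reply does not remove the point, because the wrong figure is the only significance threshold that the analysis section gives. It is also a figure stated wrongly, so it cannot be excused as a detail left to an analysis plan that is not shown.

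A reader might infer stronger claims, which the article does not support:

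- **That an ineffective booklet would have a 50% chance of being declared effective.** The test is two-tailed. Half of the false rejections would favour the control condition, so the figure is 25% per test.
- **That the trial is wrongly sized or underpowered.** The 64 per group is correct for the inputs stated, and at alpha 0.5 the nominal power would be higher than planned.
- **That the Sample size section itself specifies a two-tailed test.** It gives only 0.05. The two tails come from the Statistical analyses section and from the fact that 64 reproduces that way.

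**Conclusion.** The point holds as an internal contradiction that must be corrected. It is an error in one printed figure and leaves the design intact. The tenfold discrepancy needs no assumption beyond the text. The 50% and 25% rates need only a valid, symmetric two-tailed test and literal use of 0.5, and they apply per test. That 0.5 stands for 0.05 is an inference, though a strong one, from the reproduction of 64 per group. The SD thresholds and the power figure rest on a two-sample t-test and, for 85 per arm, also on an equal split and 15% dropout.

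**What to change.** In Statistical analyses, replace the two-tailed alpha of 0.5 with a two-tailed alpha of 0.05. Issue this as a dated correction before the first participant is recruited; the Trial status section says that recruitment has not yet started. In Sample size, add that the alpha of 0.05 is two-tailed.

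The cost is one figure and one word. The 64 per group and the recruitment target ("a total of 200 participants will be recruited for the RCT") stay as they are, and no procedure or schedule is affected.

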## Methods/design

### Design

To evaluate the effectiveness of an intervention recently developed for PLH in Botswana, an RCT will be performed. The trial will have two conditions: an intervention group, who will receive the self-help program with coaching for depressive symptoms, and an attention-only control group, who will receive the self-help program without coaching following completion of the follow-up measurement. Random allocation of participants to the intervention or control group will be performed using a stratified random sampling technique. The sample will be stratified according to gender and treatment center. It is important to stratify by gender to ensure approximately equal proportions of males and females in the intervention and control groups. In the study by [name] et al. that investigated intervention targets for depressive symptoms among PLH in Botswana, more females participated compared to males. Additionally, treatment centers are expected to differ with regard to the number of patients included; therefore, stratification will ensure that both the intervention and control groups in large and small treatment centers have almost the same numbers of patients in both conditions.

Random number tables will be used to allocate participants to either condition; these will be computer generated and produced by an independent researcher. Randomization will be done in permuted blocks of six. The independent researcher will enter the numbers into an Excel file which will conceal the randomization until after the participants are established in the trial. The randomization is set up such that the main researcher is unable to see treatment allocation beforehand, minimizing bias. Participants and coaches will not be blinded to allocation to conditions. Participant allocation to one of the conditions will be done after the pre-test.

The study is approved by the Health Research Development Committee of the Ministry of Health in Botswana (Ref. HPDME 13/18/1). The Standard Protocol Items: Recommendations for Interventional Trials (SPIRIT) checklist is provided as Additional file 1.

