**Fig. 1 Fig1:**
[figure not shown]
Flowchart of the study design

In Botswana, the majority of patients who have been on treatment for more than a year visit the treatment center once every 6 months; therefore, the screening will be conducted over a period of approximately 6 months. Any patient who obtains a score > 0 on the PHQ-2 and who meets the inclusion criteria may be referred to the researchers. The HIV consultants will provide written information about the study to the patients and request for permission to provide the researchers with the patient’s contact information (telephone number or email). Following contact with the patients, the researchers will provide further information to the patients and conduct extensive screening for depressive symptoms using the PHQ-9 by telephone. Patients with a score within the mild (> 4) and moderate (< 20) ranges will be eligible for participation in the trial. These patients will then be invited to participate. Those who agree to participate will give consent by a text message to the researchers. Additionally, we will seek permission from patients to inform a medical doctor or general practitioner at the HIV treatment center about their participation in the study. Participants will then undergo a pre-test (T0). Thereafter, the participants will be randomly assigned to the intervention or the control (attention-only) group. The coaches will call all participants at the beginning of the intervention to assess for and stimulate their motivation. This will be accomplished through the use of motivational interviewing and general conversational techniques, providing information about the program, helping the patients plan for the lessons, and advising them to engage in a small activity to get started.

The intervention group will then receive the self-help treatment program with coaching by telephone, while the control group will only receive attention through a weekly telephone chat from a coach. The participants will work on the intervention for 6 weeks (with a maximum extension of 2 weeks). During the intervention, participants will be asked to answer standardized questions at three different times. At 8 weeks, all participants will complete the post-test (T1) and subsequently the follow-up measurement (T2) 3 months later. After the follow-up, participants in the control condition will receive the intervention.

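### As written, the primary model has no group-by-time term, so it averages the zero pre-test difference into the treatment effect and estimates neither the post-test nor the follow-up difference.

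*Protocol article*

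**What the plan says.** All of the model text is in the Statistical analyses section of the protocol article.

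- Aim: "Differences between groups in depressive symptoms from pre-test to post-tests will be investigated using longitudinal multilevel regression analyses (LMRAs".
- Fixed part: "We will adopt a two-level model where time and group will be included as fixed effects".
- Random part: "the slopes for time and the intercept as random effects".
- Waves: "The between-group analysis will include the pre-test, post-test, and follow-up".
- Long-term effect: "To investigate the long-term effects of the intervention, we will include the pre-test, post-test, and follow-up in the within-group analysis".

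Two statements elsewhere bear on the point. Under Design: "Participant allocation to one of the conditions will be done after the pre-test". Under Procedure: "After the follow-up, participants in the control condition will receive the intervention".

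No group-by-time term, baseline adjustment or contrast at a named wave appears in the article.

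**The concern.** The aim is a difference between arms in how symptoms change after the pre-test. The listed fixed effects cannot express that. With main effects of time and group only, the arms are forced to differ by one constant amount at T0, T1 and T2. Randomisation makes the expected T0 difference zero, so the constant is pulled toward zero and takes in any chance imbalance at T0. The random time slope does not help, because it describes variation between persons and not a mean difference between arms.

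The sentence on long-term effects adds to the problem. Change within the intervention arm mixes the effect of the program with natural recovery and with regression to the mean, which is to be expected in a sample selected for a PHQ-9 score above 4. The control arm is there to separate these, and it is still untreated at T2.

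At stake are the size of the reported primary effect, its power, and whether a lasting effect can be told from one that has faded. The article extends the same approach to all secondary outcomes.

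**Working it through.** **The plan's own figure.** Sample size section: effect size 0.50, alpha 0.05, power 0.80, 64 per group. A two-sided two-sample t test has power 0.795 at 63 and 0.801 at 64 per group, so 64 is reproduced. That figure is for a 0.50 SD difference between two groups, not for the coefficient below.

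**Inputs from the article.** Waves at 0 and 8 weeks and 3 months later (about week 21); allocation after T0; 64 per group needed; 200 recruited, or 100 per arm if split equally. With the article's 15% dropout, 100 × 0.85 = 85 per arm.

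**Assumptions not in the article.** SD 1; complete data on the stated n; correlation 0.5 between waves under compound symmetry (0.4 to 0.7 as a range); for random slopes, intercept variance 0.5, residual variance 0.5 and slope variance 0.0005 to 0.001 per week².

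**Step 1: what the group coefficient estimates.** Under compound symmetry the generalised least squares weights on the three wave differences are equal.

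- Sustained effect: (0 + 0.50 + 0.50)/3 = 0.333 SD.
- Effect lost by T2: (0 + 0.50 + 0)/3 = 0.167 SD.

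With random slopes the weights move toward T0. At slope variance 0.0005 they are 0.41, 0.35 and 0.24; at 0.001 they are 0.46, 0.36 and 0.18. The sustained effect then becomes 0.295 and 0.269 SD, and the lost effect 0.173 and 0.178 SD.

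**Step 2: power for the sustained effect.** SE = √[(2/n)(1 + 2ρ)/3]; power = Φ(0.333/SE − 1.96).

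| n per arm | SE (ρ = 0.5) | Power (ρ = 0.5) | Power with random slopes |
|---|---|---|---|
| 64 | 0.144 | 0.64 | 0.51–0.43 |
| 85 | 0.125 | 0.76 | 0.63–0.54 |
| 100 | 0.115 | 0.82 | 0.70–0.60 |

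At 85 per arm, power is 0.80 at ρ = 0.4 and 0.68 at ρ = 0.7.

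**Step 3: the contrast that matches the aim.** With categorical time, group-by-time and baseline means constrained equal, the T1 contrast has expectation 0.50 and SE = √[(2/n)(1 − ρ²)] = √[(2/85)(0.75)] = 0.133. Power is Φ(0.50/0.133 − 1.96) = 0.96.

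**Step 4: would a linear group-by-time term be enough?** Fit a line to differences 0, 0.50, 0.50 at weeks 0, 8, 21 (mean 9.67). The slope is 4.83/224.67 = 0.0215 per week and the group intercept is 0.333 − 0.0215 × 9.67 = 0.125. The fitted difference at T1 is 0.125 + 0.0215 × 8 = 0.30 SD against a true 0.50, and at T2 it is 0.125 + 0.0215 × 21 = 0.58 SD. The slope term alone gives 0.17 SD at week 8. A linear interaction therefore still misfits an effect that arises by T1 and holds.

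**The case against.** The strongest reply is that the sentence names variables and is not a full list of model terms. The Ethical precautions section says that referral will enter the analysis as a covariate, and that term is not in the list either. Moderators are to be entered in the same type of model with no interaction named, although a moderator analysis needs one. The stated aim is itself an interaction target, and a journal article condenses. This stands as far as intent goes: the interaction may well be planned. It does not make the text right, because the article sets out fixed effects, random effects, waves and estimation method, and the fixed part it gives does not deliver the aim.

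Four stronger readings are tempting, and the article does not support them.

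- *That the long-term effect rests on within-group change alone.* The between-group analysis includes T2, and between-group effect sizes are planned. What remains is that the long-term wording attaches to the within-group analysis, and the between-group model as written has no T2-specific contrast.
- *That time is linear.* The article speaks of slopes for time but never says how time is coded in the fixed part. The random-slope figures and Step 4 depend on numeric time.
- *That the trial is underpowered in any case.* At 100 per arm with complete data and correlation 0.5, power is 0.82, above the 0.80 target. The 0.96 comparator comes from a more efficient estimator than the plan's own two-group calculation.
- *That false positives are inflated.* With no treatment effect at any wave, the group coefficient has expectation zero; the fault is dilution.

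**Conclusion.** The model is wrong as written. Run literally, it reports one constant group difference that includes the pre-test. A sustained 0.50 SD effect comes out at about 0.33 SD (0.27–0.30 with the assumed random-slope variances), and an effect gone by T2 at about 0.17 SD. Neither the T1 nor the T2 effect is estimated, and a small coefficient cannot be told apart as a modest lasting effect or a larger one that faded.

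The 0.33 and 0.17 need only equal weighting of the waves. The power figures rest on the assumed correlation, slope variances and retention; they fall below 0.80 at 64 and 85 per arm under correlation 0.5, but not at 100.

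A reader might infer that the sponsor will in fact run this model and publish a diluted effect. The article does not show that. The finding is that the stated model contradicts the stated aim and should be corrected before anyone analyses to it.

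**What to change.** Restate the primary model with time as categorical (T0, T1, T2) and a group-by-time term, with the pre-test either adjusted for as a covariate or its mean constrained equal across arms. Name the between-group contrast at T1 as the primary effect and the between-group contrast at T2 as the long-term effect. Report within-group change as descriptive. An unstructured within-person covariance is a reasonable option but is not needed to correct the error.

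The cost is wording in the analysis plan: same data, same participants, no new software. The Trial status section says recruitment had not started, so the change could be made before any outcome data existed.
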